### 10.3. Withdrawal From the Study

A subject will be withdrawn from the study for any of the following reasons:

- Lost to follow-up
- Withdrawal of consent
- Death

If a subject is lost to follow-up, every reasonable effort must be made by the study site personnel to contact the subject and determine the reason for discontinuation/withdrawal. The measures taken to follow up must be documented.

When a subject withdraws before completing the study, the reason for withdrawal is to be documented in the CRF and in the source document. Study drug assigned and dispensed to the withdrawn subject may not be assigned to another subject. Subjects who withdraw will not be replaced.

### Withdrawal From the Use of Samples in Future Research

The subject may withdraw consent for use of samples for research (refer to Section 16.2.5, Long-Term Retention of Samples for Additional Future Research). In such a case, samples will be destroyed after they are no longer needed for the clinical study. Details of the sample retention for research are presented in the main ICF.

## 11. STATISTICAL METHODS

Statistical analysis will be done by the sponsor or under the authority of the sponsor. A general description of the statistical methods to be used to analyze the efficacy and safety data is outlined below. Specific details will be provided in the Statistical Analysis Plan.

The analysis population is the intent-to-treat (ITT) population. The ITT population will include all subjects who took at least one dose of study medication.

Planned interim analyses are described in Section 11.5.

The primary analysis will be performed when all subjects infected with genotype 1 HCV who were eligible for and assigned to a total treatment duration of 12 weeks have completed the Week 24 visit (SVR12) or discontinued earlier.

The final analysis will be performed when all subjects have completed the last study-related visit (Week 36 or Week 48 depending on total treatment duration) or discontinued earlier.

For definitions, see Definition of Terms.

### 11.1. Subject Information

For all subjects who receive at least 1 dose of study drug descriptive statistics will be provided. All demographic characteristics (e.g., age, height, weight, BMI, race, ethnic origin) and other initial subject characteristics (physical examination, medical and surgical history, concomitant diseases, baseline HCV RNA) will be tabulated and analyzed descriptively.

### 11.2. Sample Size Determination

The primary efficacy parameter is SVR12 for subjects infected with genotype 1 HCV who were eligible for and assigned to a total treatment duration of 12 weeks.

One hundred and fifty subjects with genotype 1 HCV infection and with fibrosis stages ranging from equivalent to F0 to equivalent to F2 will be treated. With the assumption 50% will have genotype 1a HCV infection and 50% genotype 1b, and with estimated *IL28B* genotype breakdown being 30% CC, 55% CT and 15% TT, it is expected 69% (104 subjects) will have a Week 2 response and reach RVR and be eligible for a total treatment duration of 12 weeks.

The minimally acceptable response rate (SVR12 in subjects eligible for and assigned to 12 weeks of treatment) is taken as 80%, whilst the target response rate is 90%. With an  $\alpha=0.05$ , and a sample size of 104, based on these assumptions, the calculated power would be 90.6%. As the N is assumed, several scenarios are presented below:

| N   | Target Response | Power |
|-----|-----------------|-------|
| 96  | 90%             | 83.9% |
| 104 | 90%             | 90.6% |
| 112 | 90%             | 90.8% |

In addition, 75 subjects with genotype 4 HCV infection and with fibrosis stages ranging from equivalent to F0 to equivalent to F2 will be treated. With the assumption the estimated *IL28B* genotype breakdown will be 30% CC, 55% CT and 15% TT, it is expected 69% (52 subjects) will have a Week 2 response and reach RVR and be eligible for a total treatment duration of

12 weeks. With a target response rate of 90%, 52 subjects will allow the response rate to be estimated with a 2-sided 95% CI width of 18.1%: 90% (78.5%, 96.6%).

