There is an emerging body of evidence that in selected patient groups demonstrating very fast on-treatment response, 12 weeks of treatment with a combination of P/R and direct-acting antivirals will result in very high response rates. Two recent studies compared 12 with 24 weeks of such combinations in patients with fast viral response and found no significant difference in response rates. CONCISE included previously untreated or relapsed patients with GT1 HCV, with no to severe liver fibrosis (F0-3) and the IL28B CC genotype. Patients that had undetectable viral load after 4 weeks of triple therapy with telaprevir + P/R were randomized to either stop all treatment after 12 weeks or to extend treatment with P/R to 24 weeks. Very high cure rates were seen in both arms (SVR12: 87% vs 97%) with no statistical significant difference between arms. Another study included treatment-naïve HCV GT1 patients with no to severe liver fibrosis regardless of IL28B genotype. Patients were treated with a combination of 2 DAAs

and P/R. Patients with HCV RNA below the lower limit of detection (LLOD; 25 IU/ml) at Weeks 2 and 4 of treatment and undetected HCV RNA at Week 8 were randomized to stop all treatment at Week 12 or extend treatment to 24 weeks. Both arms showed very high response rates that did not significantly differ from each other (SVR12: 86% vs 92%). The single-arm study NEUTRINO investigated the safety and efficacy of a fixed treatment duration of 12 weeks of triple therapy with the polymerase inhibitor sofosbuvir in combination with PegIFN/RBV in patients with HCV genotype 1, 4, 5, or 6. SVR12 rates in genotype 1 and 4 were 89% and 96%, respectively. Patients responded very fast to therapy with 91% of patients having <25 IU/ml at treatment week 2. This observation further underscores the association between rapid viral response and the ability to shorten treatment without compromising efficacy and cure rates.

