### **11.3. Efficacy Analyses**

For a list of primary and secondary endpoints, see Section 9.2.2, Endpoints.

For the primary endpoint, SVR12 in subjects with genotype 1 HCV infection who were eligible for and assigned to 12 weeks of treatment, a one-sided test with  $\alpha=0.05$  will be used to compare the observed response rate to the minimally acceptable response rate of 80%.

For all proportions listed in Section 9.2.2, Endpoints, 2-sided 95% confidence intervals will be constructed around the observed response rate.

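### At the planned N of 104, the stated 90.6% power needs a success cut-off whose true one-sided error is 5.6%; held to 5%, power is 84.5%

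*Protocol*

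**What the plan says.** Section 11.2 of the protocol, repeated in the Synopsis, sets the minimally acceptable and target SVR12 rates for genotype 1 subjects assigned to 12 weeks: the first "is taken as 80%, whilst the target response rate is 90" per cent. Of 150 treated subjects, "it is expected 69% (104 subjects) will have a Week 2 response and reach RVR and be eligible" for the short course. With alpha 0.05 and "a sample size of 104, based on these assumptions, the calculated power would be 90.6" per cent. Because N is uncertain, a small table gives 83.9% at N=96, 90.6% at N=104 and 90.8% at N=112, all at a true rate of 90%.

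Section 11.3 fixes the level and direction: "a one-sided test with $\alpha=0.05$ will be used" for the comparison with 80%. Neither section names the test, the number of responders needed, or the type I error attained at any N.

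**The concern.** The table moves oddly. Power rises 6.7 points for the first 8 extra subjects (83.9% to 90.6%) and 0.2 points for the next 8 (90.6% to 90.8%). Jumps of this kind are normal for a binomial count, but here they raise the question of whether every row is held to the same error rate.

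This is the only formal hypothesis test in the protocol, and N=104 is the row on which the trial is planned. If that row's power is available only when the stated 5% level is exceeded, a reader of Section 11.2 is told of a combination of error rate and power that the design cannot deliver at that N. In addition, a result of exactly 90 of 104 would be a success under one common test and a failure under another, with nothing in the protocol to decide between them.

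**Working it through.** **Inputs.** Null rate 0.80, target rate 0.90, alpha 0.05 and N = 96, 104, 112 from Section 11.2; one-sided testing from Section 11.3. The planning N is 0.69 × 150 = 103.5, rounded to 104. Let X be the number of responders, binomial with size N.

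**Reproducing the plan's figures.** An uncorrected one-sample z-test rejects when (X/N − 0.80) / √(0.80 × 0.20 / N) is at least 1.645, that is, when X ≥ N × (0.80 + 1.645 × √(0.16/N)).

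- N=96: bound 83.2, so the cut-off is 84. P(X ≥ 84 | 0.90) = 0.8391.
- N=104: √(0.16/104) = 0.03922, bound 89.9, so the cut-off is 90. P(X ≥ 90 | 0.90) = 0.9055.
- N=112: bound 96.6, so the cut-off is 97. P(X ≥ 97 | 0.90) = 0.9078.

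These round to 83.9%, 90.6% and 90.8%, the three tabulated values. Other usual formulas do not give all three; at N=104, for example, the one-sided normal-approximation score formula gives 88.6%, the arcsine formula 89.4% and the continuity-corrected formula 85.2%.

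**True type I error of those cut-offs**, P(X ≥ cut-off | 0.80), beside the smallest cut-off with true error at or below 0.05:

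| N | z-test cut-off | True size | Power | Exact-test cut-off | True size | Power |
|---|---|---|---|---|---|---|
| 96 | 84 | 3.83% | 83.9% | 84 | 3.83% | 83.9% |
| 104 | 90 | 5.64% | 90.6% | 91 | 3.17% | 84.5% |
| 112 | 97 | 4.67% | 90.8% | 97 | 4.67% | 90.8% |

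The two tests coincide at 96 and 112 and differ by one responder at 104. At 90/104, z = 1.667 with nominal p = 0.048, while the exact one-sided p-value is 0.056. That one responder carries 5.64 − 3.17 = 2.47 points of size and 90.55 − 84.49 = 6.06 points of power. Held to an exact 5% level, the table would read 83.9%, 84.5%, 90.8%.

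**Allowing for the uncertain N.** Assume N follows a Binomial(150, 0.69) distribution, the protocol's own eligibility proportion, and average over it:

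- exact test: size 3.7%, power 85.8%;
- uncorrected z-test: size 4.5%, power 87.9%.

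Under either test the expected power is below 90%.

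**The case against.** The strongest defence is that the calculation contains no mistake. One rule produces all three rows, it is a standard test, and at 90 of 104 it does reject at a nominal 0.05; a mid-p test would also reject there (mid-p 0.044). The protocol does not name the test and leaves details to the statistical analysis plan. The exact test is conservative, with a size of 3.2% at this N. N=104 exactly has only about a 7% chance of occurring, and averaged over N the z-test's true size is 4.5%, below 5%. The section also says openly that N is assumed, and it tabulates 83.9% at N=96.

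Most of this stands. A reader might infer an arithmetic slip, or that the table mixes methods; neither is so. Nor is leaving the test unnamed a fault in itself. What remains is that Section 11.2 quotes one power figure at one N beside an alpha of 0.05, and at that N the figure requires an error of 5.6%. Averaging over N does not rescue the headline, because it lowers the z-test's power to 87.9%.

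Three stronger readings are also tempting and are not supported:

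- **The 69% ignores the Week 8 criterion.** The sentence names only Week 2 response and RVR, but it presents 69% as the eligible proportion, and eligibility includes Week 8. The wording is short; it does not show that Week 8 was left out of the estimate.
- **Drop-out will push N below 104, for example to 99, with exact power of 81.1%.** The protocol gives no such figure. The endpoint set is those eligible for and assigned to 12 weeks, so leaving after assignment need not reduce it. N=99 also happens to be a low point for exact power: at N=100 it is 87.6%.
- **The 12-week rates of 86%, 87% and 89% cited in Section 1.6 show that the 90% target is too high.** They come from other drug combinations and from populations selected differently from this trial's F0–F2 rapid responders. They do not contradict the target.

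**Conclusion.** The point holds as a mismatch between stated alpha and stated power, confined to the planning row. At N=104 the pair of 5% and 90.6% is not attainable: the choice is 5.6% with 90.6%, or 3.2% with 84.5%. The overstatement is about 6 points of power at that N if the 5% level is taken as a strict limit, or 0.64 points of type I error if the z-test is kept. Averaged over N, the two tests differ by about 2 points of power (87.9% against 85.8%).

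The conclusion rests on reading alpha as an upper limit on the true error of a non-randomised test, and, for the averages, on a binomial N with 69% eligibility. The consequence is moderate. Power at the target rate stays above 80% under either test, and nothing here suggests that the trial is too small.

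**What to change.** In Section 11.2 and the Synopsis:

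- name the exact one-sided binomial test at alpha 0.05 as the primary test, and say the same in Section 11.3;
- replace 90.6% at N=104 with 84.5%, success being 91 or more responders of 104 (87.5%), with true size 3.2%; the N=96 and N=112 rows stay as they are;
- add that N is random and that exact power averaged over a Binomial(150, 0.69) N is about 86%.

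If the sponsor prefers the uncorrected z-test, name it instead, and disclose its 5.6% size at N=104 and its averaged power of about 88%.

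The cost is a few sentences, one table row and a less favourable headline. The target of 150 genotype 1 subjects is unchanged. The choice of test should be fixed before the primary analysis, so that a borderline count cannot decide it.

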### **11.3. Efficacy Analyses**

For a list of primary and secondary endpoints, see Section 9.2.2, Endpoints.

For the primary endpoint, SVR12 in subjects with genotype 1 HCV infection who were eligible for and assigned to 12 weeks of treatment, a one-sided test with  $\alpha=0.05$  will be used to compare the observed response rate to the minimally acceptable response rate of 80%.

For all proportions listed in Section 9.2.2, Endpoints, 2-sided 95% confidence intervals will be constructed around the observed response rate.

### **11.4. Safety Analyses**

Safety endpoints will be analysed in subjects infected with genotype 1 or genotype 4 HCV separately per genotype and for both genotypes combined.

#### **Adverse Events**

The verbatim terms used in the CRF by investigators to identify AEs will be coded using the Medical Dictionary for Regulatory Activities (MedDRA). All reported AEs with onset during the treatment phase (i.e., treatment-emergent AEs, and AEs that have worsened since baseline) will be included in the analysis. For each AE, the percentage of subjects who experience at least 1 occurrence of the given event will be summarized by treatment group.

Summaries, listings, datasets, or subject narratives may be provided, as appropriate, for those subjects who die, who discontinue treatment due to an AE, or who experience a severe or a serious AE.

All events of special interest will be evaluated in conjunction with other systemic symptoms and laboratory abnormalities: information on time of onset, duration of events, time to resolution, concomitant therapies, and relationship to TMC435, PegIFN $\alpha$ -2a, RBV, and HCV infection will be tabulated.

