##### **Reproductive Risks and Pregnancy:**

No studies with TMC435 were performed in pregnant women. In animal studies, TMC435 had no effect on fertility and early embryonic and fetal development in rats up to doses of 500 mg/kg corresponding to an exposure of 221 µg.h/mL in plasma. No human data on the effect of TMC435 on fertility are available. Therefore, pregnancy and breastfeeding have been exclusion criteria for all clinical studies with TMC435 conducted to date. Women of childbearing potential and men included in studies with TMC435 have been required to use effective methods of birth control.

Significant teratogenic and/or embryocidal effects have been demonstrated in animals exposed to RBV. Ribavirin may persist in non-plasma compartments for as long as 6 months. Ribavirin is contraindicated in females who are pregnant or breastfeeding and in male partners of females who are pregnant. Ribavirin should not be started unless a report of a negative pregnancy test has been obtained immediately prior to initiation of therapy. In addition, extreme care must be taken to avoid pregnancy in females of childbearing potential or males having a female partner of childbearing potential taking RBV for at least 6 months after completion of PegIFNα-2a and RBV therapy (or longer, if dictated by local regulations). Subjects must consent to utilize 2 effective methods of birth control (as specified in Section 4.3), and male adolescents should not donate sperm while participating in this study and for at least 6 months after receiving the last dose of RBV (or longer, if dictated by local regulations; see Section 4.3 for more detail).

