**Figure 1: Schematic Overview of the Study**

**All subjects:** 12 weeks of triple therapya; stop all therapy after Week 12 if  
HCV RNA < 25 IU/mL (detectable or undetectable) at Week 2 AND  
< 25 IU/mL undetectable at Week 4 AND  
< 25 IU/mL undetectable at Week 8;  
otherwise continue treatment in Extension

[figure not shown]**Treatment Extension**

If HCV RNA at Week 2, 4 and 8 does not meet the above-outlined criteria for treatment stop at Week 12, the subject should continue PegIFN/RBV until Week 24a

[figure not shown]

a unless a virologic stopping rule is met, see Section 6.3, Virologic Stopping Criteria for further details

b primary endpoint

c secondary endpoint

TMC435 will be taken as oral capsules of 150 mg. PegIFN $\alpha$ -2a and RBV will be given as Pegasys and Copegus (see Section 6.2, Timing of Dosing for further details). Pegasys and Copegus will be administered according to the manufacturer's prescribing information. Pegasys (180  $\mu$ g once weekly) will be administered as weekly subcutaneous (SC) injections of 0.5 mL. The total daily dose of Copegus is weight-dependent. If body weight is < 75 kg, the total daily dose is 1000 mg, administered as 400 mg (2 tablets of 200 mg, morning intake) and 600 mg (3 tablets of 200 mg, evening intake). If body weight is  $\geq$  75 kg, the total daily dose is 1200 mg, administered as 2 x 600 mg (3 tablets of 200 mg per intake, morning and evening).

The study will be conducted in 3 phases: a screening phase of maximum 6 weeks, a treatment phase extending from Day 1 (baseline) up to 12 or 24 weeks depending on the response to treatment, and a posttreatment follow-up period of 24 weeks after the subject's last planned dose of study drug. The duration of the subject's participation (excluding screening phase) will vary between 36 weeks and 48 weeks, depending on the response to treatment.

Subjects should maintain the study visit schedule during treatment interruptions or after premature treatment discontinuation as outlined in the Time and Events Schedule. Additional unscheduled visits may be performed for safety or tolerability reasons if needed.

Interim analyses will be conducted (refer to Section 11.5, Interim Analyses).

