| All subjects
stop all therapy after Week 12 if
HCV RNA < 25 IU/mL (detectable or undetectable) at Week 2 AND
< 25 IU/mL undetectable at Week 4 AND
< 25 IU/mL undetectable at Week 8;
otherwise continue treatment in Extension                                                                                                          |                                                                                                                                                                                                                                       |                                                                                                                                                                                                                                         |
| Week 1 (Day 1) to Week 12 (Day 84) (inclusive)                                                                                                                                                                                                                                                                                                                               | 
 
• TMC435: 150 mg q.d., oral
 
• PegIFN<math>\alpha</math>-2a: 180 <math>\mu</math>g once weekly, SC
 
• RBVa: 1000 mg or 1200 mg in a b.i.d. regimen, oral
 
 | 
 
• TMC435: one 150-mg capsule
 
• PegIFN<math>\alpha</math>-2a: 1 SC injection of 0.5 mL
 
• RBV: 200-mg tablets as needed according to the subject's weighta
 
 |

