**12.3. Procedures****12.3.1. All Adverse Events**

All AEs and special reporting situations, whether serious or non-serious, will be reported from the time a signed and dated ICF is obtained until 4 weeks after last study medication intake. Thereafter, only AEs considered related to TMC435 will be reported. Serious adverse events, including those spontaneously reported to the investigator within 30 days after the last study-related procedure, must be reported using the Serious Adverse Event Form. The sponsor will evaluate any safety information that is spontaneously reported by an investigator beyond the time frame specified in the protocol.

All AEs, regardless of seriousness, severity, or presumed relationship to study drug, must be recorded using medical terminology in the source document and the CRF. Whenever possible, diagnoses should be given when signs and symptoms are due to a common etiology (e.g., cough,

runny nose, sneezing, sore throat, and head congestion should be reported as "upper respiratory infection"). Investigators must record in the CRF their opinion concerning the relationship of the AE to study therapy. All measures required for AE management must be recorded in the source document and reported according to sponsor instructions.

The sponsor assumes responsibility for appropriate reporting of AEs to the regulatory authorities. The sponsor will also report to the investigator (and the head of the investigational institute where required) all SAEs that are unlisted (unexpected) and associated with the use of the study drug. The investigator (or sponsor where required) must report these events to the appropriate Independent Ethics Committee/Institutional Review Board (IEC/IRB) that approved the protocol unless otherwise required and documented by the IEC/IRB.

Subjects (or their designees, if appropriate) must be provided with a "study card" indicating the following:

- Subject's name
- Study number
- Investigator's name and 24-hour contact telephone number
- Sponsor's name and 24-hour contact telephone number
- Statement, in the local language(s), that the subject is participating in a clinical study.

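### AE incidence percentages are tied to onset in the treatment phase, so ordinary AEs collected in the 4 weeks after the last dose enter no planned percentage

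*Protocol*

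**What the plan says.** Section 11.4 (Adverse Events) gives the rule for the AE analysis: "All reported AEs with onset during the treatment phase (i.e., treatment-emergent AEs, and AEs that have worsened since baseline) will be included in the analysis". The next sentence plans, for each AE, the percentage of subjects with at least one occurrence. The Synopsis (Safety) repeats the rule, again taking "All reported AEs with onset during the treatment phase".

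The phases are set out in Section 3.1 and in the Synopsis design overview. After screening there is "a treatment phase extending from Day 1 (baseline) up to 12 or 24 weeks depending on the response to treatment", and then "a posttreatment follow-up period of 24 weeks after the subject's last planned dose of study drug". Table 1 puts the last dosing day at Day 84 for the 12-week course and Day 168 for the extension.

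Collection runs longer than the treatment phase. Section 12.3.1 has all AEs reported from consent "until 4 weeks after last study medication intake", and after that only those considered related to TMC435. Section 9.5.1 says the same and adds that serious AEs are reported to 30 days after the last study-related procedure.

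Section 11.4 also describes two outputs that carry no phase restriction. One is summaries, listings or narratives for deaths, AE discontinuations and severe or serious AEs, which the protocol words as optional. The other is a tabulation of events of special interest, which it words as required.

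**The concern.** The window for collecting AEs and the window for counting them do not match, and nothing in the protocol reconciles them. The sites are asked for every AE over the 4 weeks after treatment, with a visit at the end of that period (Week 16 or Week 28 in the Time and Events Schedules). The only planned AE percentage stops at the end of the treatment phase.

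Safety and tolerability of the 12-week regimen in genotype 1 is a primary objective (Section 2.1), and the Synopsis gives fewer side effects as one reason for shortening treatment. If ordinary AEs arise or worsen just after the last dose, the headline safety table would miss them although the data are in the database.

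**Working it through.** The protocol states no figure to reproduce. The check is a comparison of windows, followed by an illustration of size.

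**Step 1. Windows for a subject who completes treatment**
- Onset window for the percentages (11.4 with 3.1 and Table 1): Day 1 to Day 84, or Day 1 to Day 168.
- Collection window for all AEs after first dose (12.3.1): the same period plus 4 weeks, so 12 + 4 = 16 weeks or 24 + 4 = 28 weeks.
- First onset day outside the percentages: Day 85 or Day 169.

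**Step 2. Share of collection time left out**, 4 / (T + 4), with T the weeks of treatment
- T = 12: 4 / 16 = 25.0%.
- T = 24: 4 / 28 = 14.3%.

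**Step 3. What happens to events that start after the treatment phase**
- Ordinary AEs in the first 4 weeks: collected, in no planned percentage.
- TMC435-related AEs in the remaining 24 − 4 = 20 weeks of follow-up: collected, in no planned percentage.
- Deaths and serious or severe AEs: optional outputs only, unless they are events of special interest.
- Events of special interest: tabulated, with no phase limit stated.
- Laboratory abnormalities, vital signs and examination findings: summarised at each scheduled time point (11.4). Patient-reported scores: change from baseline through follow-up (9.2.2).

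**Step 4. How much a percentage could move.** This rests on assumptions, since the documents give no post-dose AE rate for this regimen. Let p be the on-treatment cumulative incidence and f the hazard in the 4 post-dose weeks relative to the on-treatment hazard, with f from 0 to 1. On a constant on-treatment hazard, incidence over the longer window is 1 − (1 − p)^((T + 4f)/T).
- p = 10%, T = 12: 10.0% (f = 0), 11.6% (f = 0.5), 13.1% (f = 1).
- p = 10%, T = 24: 10.0%, 10.8%, 11.6%.
- p = 20%, T = 12: 20.0%, 22.9%, 25.7%.
- p = 20%, T = 24: 20.0%, 21.5%, 22.9%.

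The lower end of every range is no change at all.

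**Step 5. Subjects who stop early.** Section 3.1 describes the treatment phase in planned weeks and counts follow-up from the last planned dose. For a subject who stops all drugs before that, the text does not say whether the treatment phase ends at the last dose taken or at the planned end. The same AE could be counted or not depending on the reading.

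**The case against.** The strongest reply is that the analysis plan settles this. Section 11 calls itself a general description and leaves specifics to the SAP, which is not at hand, and the number of post-dose days in a treatment-emergent flag is a common SAP detail. The protocol also says that treatment-phase AEs will be included; it never says that others are excluded. Part of this stands: exclusion is the plain reading rather than an explicit statement, and a SAP could widen the window. But the protocol did not leave the window open. It names the treatment phase in two places, equates that with treatment-emergent, and plans no other AE percentage. A SAP that widens the window departs from that wording; one that follows it keeps the gap.

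The second reply is that late toxicity is not lost. This stands in large part. Hematology, TSH, the depression scale and physical examination continue in follow-up and are summarised there, and the special-interest tabulation is mandatory. These are not AE incidence tables, but they narrow what could go unseen.

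Three stronger readings are tempting and are not supported:
- **That 25% and 14% measure missed events.** They are shares of weeks. They would translate into incidence only if the hazard off drug matched that on drug, which nothing in the protocol shows.
- **That the gap distorts a comparison of 12 with 24 weeks.** Section 11.4 plans safety by genotype and combined, not by duration. Duration is set by virologic response, so such a comparison would be confounded under any window.
- **That residual exposure proves an event rate.** Section 1.5.4 does say "Ribavirin may persist in non-plasma compartments for as long as 6 months", but in the context of contraception. The TMC435 half-life of 41.3 hours in infected subjects (Section 1.2) was observed at 200 mg rather than 150 mg. In 24-week subjects TMC435 stops at Week 12, so its washout falls inside the treatment phase. These points make post-dose exposure plausible and say nothing about how many AEs follow.

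**Conclusion.** The point holds in a limited form. As written, the AE percentages for completers stop at Day 84 or Day 168, while collection of all AEs runs 4 weeks longer. Ordinary AEs with onset in those weeks enter no planned AE percentage. The gap is 4 of 16 collection weeks for 12-week subjects and 4 of 28 for 24-week subjects.

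The resulting under-count is unknown. It is zero if no new subjects have a first occurrence after dosing, and on the assumed rates above it is at most a few percentage points for a given AE (5.7 points at p = 20%, T = 12, f = 1). The conclusion rests on reading the treatment phase in Section 11.4 as the one defined in Section 3.1, and on the absence of any other AE percentage in the protocol. It does not extend to a claim that late safety data go unanalysed. For early stoppers the end of the phase is unclear rather than wrong. Because safety is a primary objective and the data are already collected, the mismatch is worth correcting, as a modest improvement rather than a flaw that threatens the trial.

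**What to change.** In Section 11.4 and the Synopsis, define treatment-emergent AEs as those with onset or worsening from the first dose to 4 weeks after the last actual intake of any study medication. Base the AE percentages on that set. Anchoring to actual intake also settles the window for subjects who stop early. Tabulate separately the serious AEs and the TMC435-related AEs with onset after that window, labelled as follow-up. Carry the same definition into the SAP.

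The cost is wording and one additional table. Collection, visits, dosing and clinical rules do not change. AE percentages may come out slightly higher than under the present wording.
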